**Fig. 2 Fig2:**
[figure not shown]
Estimated number of pupils tested annually, assuming no dropouts. Dark grey is intervention schools, light grey control schools

**Table 2 Tab2:** Test variables for HOPP

Annual test methods	Grades
Activity & health	
Physical activity monitoring	All
Fitness tests^b^	All
Oxygen uptake^c^	1^st^
Blood samples^d^	All who volunteered
Learning & cognition	
Erikson Flanker test	2^nd^
Stroop test	4^th^, 5^th^ & 6^th^
Academic national tests	5^th^
Nutrition and growth	
Diet (“Ungkost 2000”)	4th
Anthropometry	All
Body composition^a^	All
Mental health	
Life Quality in Children and Adolescents (ILC)	All
Strengths and Difficulties Questionnaire (SDQ) (2016)^e^	6^th^ & 7^th^
Self-Perception Profile for Adolescents (SPPA) (2016)^e^	6^th^ & 7^th^

^a^= Using Tanita bio-impedance measurements.

^b^= Fitness tests include endurance test (Andersen test), strength (handgrip) and balance.

^c^= Oxygen uptake was performed on 1st grade pupils only as it is very time consuming.

^d^= Blood samples include serum cholesterol, High-density Lipoprotein (HDL), Ferritin, Iron, Cobalamin (total vitamin B12), Holotranscobalamin (active vitamin B12), Creatinine, HS-CRP, blood count, Haemoglobin, Hematocrit and HbA1c.

^e^= SDQ & SPPA are tested as of 2016.

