### Outcome measures

The tests were supervised by the principal investigator, and conducted by students from the Kristiania University College, Institute of Health Sciences, Oslo, Norway. All students were trained before administrating the tests. All tests were performed at the elementary schools.

All pupils in 1st to 6th grade (6–11 years) recruited in 2015 are followed longitudinally from baseline in spring 2015 for as long as they stay in elementary school. Hence, 1st grades in 2015 are followed until 2021, though 6th grade is followed for one year. This implies an annually decline in the number of participants in the research project as the eldest pupils moves on to junior high school (Fig. 2). The implementation of the intervention started fall 2015. Due to ^1)^ time limitations, ^2)^ the total test load at each grade and ^3)^ age specific tests, some tests were limited to certain age groups, as shown in Table 2. In Fig. 3 the cumulative number of all tests at each grade throughout the length of the study is shown.

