### Tests not taken annually

Due to time restraints, suitability and validation some tests were conducted only at specific ages. Eriksen Flanker test for executive functions is validated up to 3rd grade. Older pupils used the Stroop test. Also, the Strength and Difficulties Questionnaire (SDQ), Self-Perception Profile for Adolescents (SPPA), the nutrition test and academic performance, were all used in specific age groups. Effects of the intervention will be investigated in regards to these test outcomes as well as secular trends over time. Also, the results will be compared to reference materials.

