#### SDQ, SPPA and friendship nomination

The Strengths and Difficulties Questionnaire (SDQ), The Self-Perception Profile for Adolescents (SPPA) and friendship nomination were given digitally under supervision to pupils in 6^th^ and 7^th^ grades, using Questback. SDQ is a behavioural screening questionnaire for 2–17 year olds inquiring 25 positive and negative attributes [41]. SDQ is divided in five scales, each with five items; emotional symptoms, conduct problems, hyperactivity/inattention, peer relationship problems and pro-social behaviour. The first four items are added together to generate a total difficulties score. SDQ reflects levels of internalizing and externalizing psychopathology within a Norwegian child population [41–44].

SPPA has been widely used in research related to self-concept [20]. The revised version of SPPA was used in the Young in Norway study [45]. The SPPA consist of five items, each rated on a Likert-scale.

Children’s best friend nominations are thought to represent the peers with whom participants affiliate the most strongly [46]. Having close friends during childhood has been linked to improved mental health and resilience in later life [46]. Friendship will be evaluated by use of «best friend» nomination, including the listing of current friends and three best friends [47]. Also, the children will be asked to justify the reason for someone being their best friend. These answers will be organized into different categories as suggested by Thorpe et al. [48].

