#### Analyses of effect

Establishing a baseline in 2015 permits a paired comparison of results in 2016, meaning one-year effect analyses of intervention on multiple variables as described in Table 2. The analyses would include test *within-subject* variation as well as *between-subject* variation for both intervention and control schools using basic univariate parametric tests as e.g. t-tests, linear or logistic regression analysis and linear mixed models for repeated measurements. Possible confounding, mediation and/or effect modification will be assessed using stratified and multivariable statistical models and statistical methods for causal inference (e.g. Directed Acyclic Graphs).

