#### Analyses of longitudinal effect

The longitudinal intervention design allows for exploratory analysis of group means over time to discover patterns of systematic variation across groups, as well as among individuals. The design allows for analyses of age and growth effects [50]. As the eldest pupils enrolled at baseline 2015 finish elementary school in 2016, only one year of follow-up is possible. However, an increasing number of years of follow-up are possible with decreasing age at enrolment. This allows for an adjustment of the longevity of being enrolled in the program, and hence measurement of the time-in-the-program effect. Secondly, an annual comparison between the intervention schools and the control schools allows for testing of effect of the intervention. Thirdly, mean values across test time allows for time slopes showing possible effect as an interaction (i.e. effect modification) of intervention and time. A different approach for test across test time may be pre-post analysis of a single follow-up response in conjunction with a baseline measurement [50]. Fourthly, an annual comparison with the upcoming grade within the intervention schools allows for analyses of secular trends.

The longitudinal design in the HOPP study with repeated measures allows for use of a linear mixed regression model using test-year, years of follow-up, intervention versus control school, age and gender as fixed factors for the main outcome of cardio-metabolic risk factors. A similar model may be used for secondary outcomes of academic performance, PA level, cognitive performance, as well as medical and physical results, and simultaneously controlling for baseline values. In addition, the design admits analyses of interaction (i.e. effect modification) between type of intervention group and number of years in intervention.

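### SDQ and SPPA have no pre-programme value in either arm, so the intervention effects foreseen for them cannot be baseline-adjusted or cover the first year

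*Protocol article*

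**What the plan says.** The section Outcome measures says that pupils recruited in 2015 are "followed longitudinally from baseline in spring 2015 for as long as they stay in elementary school", and then: "The implementation of the intervention started fall 2015". Table 2 marks the SDQ and SPPA rows with the year 2016 and repeats in footnote e: "SDQ & SPPA are tested as of 2016". The section on SDQ, SPPA and friendship nomination says that they "were given digitally under supervision to pupils in 6^th^ and 7^th^ grades, using Questback".

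The section Tests not taken annually lists SDQ and SPPA among the age-specific tests and continues: "Effects of the intervention will be investigated in regards to these test outcomes as well as secular trends over time". Analyses of effect pairs the 2015 baseline with 2016, "meaning one-year effect analyses of intervention on multiple variables as described in Table 2". Analyses of longitudinal effect says a mixed model may be used for secondary outcomes, "simultaneously controlling for baseline values". It also describes analyses of time in the programme and of the interaction between group and years of intervention.

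Two other passages bear on the point. The section National academic tests states outright that a one-year intervention effect cannot be measured for those tests. Limitations of the study says that, for age-specific tests, only a limited number of participants can contribute to an effect analysis and that secular trends will be used instead.

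**The concern.** An intervention effect in a non-randomised comparison usually depends on knowing where each arm started. For SDQ and SPPA nobody knows, because the first measurement comes after the start in both arms. The protocol says this plainly for the national tests but not for these two questionnaires, for which it foresees effects.

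Mental health is listed in the Abstract as a secondary outcome separate from quality of life, and the Discussion names the SDQ as its instrument and the SPPA as the body-image questionnaire. The seven intervention schools and the two control schools lie in different counties. The controls were chosen on estimated socioeconomic level, not on mental health. If a post-start arm difference is reported as a programme effect, any difference that existed before fall 2015 is included in it, in either direction.

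**Working it through.** The protocol gives no figure to reproduce here: Table 3 has no row for SDQ, SPPA or mental health. The check is a count of test years by cohort.

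**Inputs.** Cohort sizes come from Table 1. Tests are given in grades 6 and 7, from 2016 onward. The programme starts in fall 2015. A pupil in grade g in spring 2015 is in 6th grade in 2015 + (6 − g) and in 7th grade in 2015 + (7 − g). Years before 2016 are dropped, and no dropout is assumed.

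| Born | Grade in 2015 | Intervention | Control | SDQ/SPPA years | Values before fall 2015 |
|---|---|---|---|---|---|
| 2003 | 6 | 271 | 154 | 2016 | 0 |
| 2004 | 5 | 269 | 112 | 2016, 2017 | 0 |
| 2005 | 4 | 264 | 125 | 2017, 2018 | 0 |
| 2006 | 3 | 229 | 141 | 2018, 2019 | 0 |
| 2007 | 2 | 264 | 117 | 2019, 2020 | 0 |
| 2008 | 1 | 248 | 103 | 2020, 2021 | 0 |
| Total | | 1545 | 752 | | 0 |

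**First wave (2016).** Intervention: 269 + 271 = 540. Control: 112 + 154 = 266. Together at most 806 pupils, all measured after the start. The 2003 cohort has one measurement. Each later cohort can have a 6th-to-7th-grade pair, but both values fall after the start, so the first of them is not a baseline.

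**What each contrast estimates.** Let G be the arm difference before fall 2015, and E(t) the programme effect in the t-th year of exposure.

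- Single comparison of 6th grades in 2016: D(2016) = G + E(1). Without a pre-programme value, G and E(1) cannot be separated.
- Change in arm difference between the 6th grades of 2016 and 2020: D(2020) − D(2016) = [G + E(5)] − [G + E(1)] = E(5) − E(1). G cancels if it is the same for both cohorts. What remains is the added effect of 2020 − 2016 = 4 further years. E(1), and with it the total effect E(5), stays unknown.
- Secular trend as defined in Analyses of longitudinal effect: a comparison with the upcoming grade within the intervention schools. That definition includes no control series, and for SDQ and SPPA no pre-programme cohort either. Taken alone, it cannot attribute a trend to the programme.

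**The case against.** Five points can be made for the protocol.

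1. **One-year effects.** A reader might infer that a paired 2015-2016 effect is promised for SDQ and SPPA. The text does not support that. The sentence in Analyses of effect is general, "one-year effect analyses of intervention on multiple variables as described in Table 2", and the table it refers to marks both tests as 2016. What stands is that the section does not expressly exclude them and that Tests not taken annually names them when it foresees effects. The baseline-controlled model is likewise only something that may be used, and it does not name these tests.

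2. **Longitudinal contrasts.** A reader might infer that every analysis carries the earlier arm difference in full. That is true of a single post-start comparison. The group-by-years contrasts, applied to successive cohorts in both arms, cancel a stable gap. This part of the objection stands, but the contrasts answer a narrower question, and nothing ties them to SDQ or SPPA.

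3. **Confounding.** The plan foresees multivariable and causal-inference methods, and controls were chosen on socioeconomic level. These may reduce bias, but they do not replace an outcome value from before the programme.

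4. **Size of the bias.** If school-level variation were 2% to 5% of total variance (an assumption; the protocol gives no value), chance differences between 7 and 2 schools would have an SD of √(0.02 × (1/7 + 1/2)) = 0.11 to √(0.05 × (1/7 + 1/2)) = 0.18 pupil SD. This is illustration only. The remark in the Discussion about small effects in earlier trials follows results on activity, screen time, oxygen uptake and cholesterol, so it is no benchmark for mental health.

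5. **What the 2016 start cost.** A reader might infer that starting in 2015 would have given every pupil a baseline. In the same grades it would have given a pre-programme value only to the 2003 cohort (271 and 154 pupils). For the others the gap follows from the age restriction, which is disclosed.

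**Conclusion.** The timing defect is certain from the protocol's own dates: 0 of 1545 intervention pupils and 0 of 752 control pupils can have a pre-programme SDQ or SPPA value. For these two tests no paired 2015-2016 or baseline-adjusted effect can be estimated, and a single post-start arm difference cannot be read as an effect. The cohort contrasts remain usable for the added effect of further years, provided that the earlier arm gap was stable across cohorts.

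The size of any bias cannot be derived from the protocol.

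A reader might also infer that all mental-health or wellbeing measurement lacks a baseline, since Table 2 puts the ILC under the same heading. It does not: the ILC is taken annually by all participants and has a true 2015 value. But the protocol treats it as the quality-of-life outcome, so it does not close the gap for the SDQ. The matter concerns secondary outcomes only. It should be corrected, and the correction is cheap.

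**What to change.** - In Tests not taken annually and Analyses of effect, state that SDQ and SPPA have no pre-programme value and exclude them from the one-year and baseline-adjusted effect analyses, in the way the national academic tests are already handled.
- Report their arm differences as exploratory, post-start associations, adjusted for each child's 2015 ILC score. State that this is a partial proxy and that earlier differences cannot be ruled out; the protocol does not show that the ILC can stand in for either test.
- Limit any effect-type inference to the change in arm difference across cohorts with increasing exposure, in both arms. State the stable-gap assumption, and that the first-year and total effects are not estimated.
- Keep the ILC as the quality-of-life outcome with its 2015 baseline. Do not substitute it for the SDQ mental-health outcome.

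The cost is some wording and one covariate already collected. The downside is that the SDQ and SPPA claim weakens from effect to association. The missing measurements cannot be recovered.

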**Fig. 3 Fig3:**
[figure not shown]
The accumulated number of annual tests at each grade is shown. Each cohort’s birth year is located within each column along with the estimated number of participants, which equals sample size. Dark grey columns are intervention schools, light grey control schools

### Children’s test

#### Annual measurements for all participants

Measurement of ^1)^ anthropometry, ^2)^ body composition, ^3)^ fitness and ^4)^ PA level, ^5)^ blood pressure, ^6)^ blood samples and ^7)^ The Inventory of Life Quality in children and adolescents (ILC) are to be completed annually for all participants (Table 3). The protocol design allows for baseline analyses, interventional one-year effect analyses, analyses of secular trends and longitudinal effect analyses across the full length of the study. Due to being very time consuming oxygen uptake is restricted to pupils born 2008 (1^st^ grade in 2015).

**Table 3 Tab3:** Based on the various power tests, the following sample size (intervention and controls schools) was calculated, with a beta of 80% and alpha of 5%

Test area	n
Anthropometry	64^b^
Cardio-metabolic risk factors	126^c^
Physical activity level	73^a^
Aerobic capacity	10^a^
General physical capacity	126^c^
Blood tests	34^a^
Quality of life	73^a^
Diet	24^a^
Cognitive ability	85^a^
Academic performance	34^a^

Statistical program: Systat 13, Power Analysis. ^a^One-sample t-test, ^b^Two-sample t-test, ^c^Z-score

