##### 8) Oxygen uptake

Only pupils born 2008 are to be tested for oxygen uptake annually until 2021 as oxygen uptake procedures require use of highly sophisticated instruments for field-testing and is time consuming. By obtaining seven consecutive years of data, longitudinal measurement of physiological development across childhood will be available. In addition, the design permits comparison between intervention (*n* = 248) and control (*n* = 103) schools for all years.

The oxygen uptake test at baseline was performed on a treadmill (Matrix T3xe, USA) measuring peak oxygen uptake (VO_2peak_), respiratory rate (RR), respiratory exchange ratio (RER), peak ventilation (VE_peak_), peak heart rate (HF_peak_) and time to exhaustion using a portable metabolic analyzer, Cosmed K4b^2^,(Cosmed S.r.l., Roma, Italia). A Hans Rudolph V2 oro-nasal facemask (Hans-Rudolph, Shawnee, KS, USA) was used during testing. The protocol in use had a start load of 5 km/h – 5% incline for 5 min. The speed was increased to 7 km/h, and further by 1 km/h every minute until reaching 10 km/h. After this point, a 1% increase in incline was applied every minute until fatigue [30, 31]. Breath by breath results was averaged to 30 s intervals and the highest 30 s value near the end of the test was considered the VO_2peak_. As test termination criteria for adults are difficult to achieve for children, the children’s unwillingness to continue was used as an indication of VO_2peak_ [32].

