##### Intervention analyses

Annually analyses between intervention and control schools in numerous variables, the sample size for a parallel group design is calculated using *n* = 2 • (σ / Δ) ^2^ • *k* [26]. Here n represents the number of participants in each group, σ (sigma) is the expected standard deviation of the observations (which are assumed equal for all groups), Δ (delta) gives us the relevant difference between observations, and k is the constant in this study chosen based on the common values by a double-sided t-test set at 5% and with test strength 80% (this corresponds to a *k* of 7.9) [26]. Based on these calculations we have determined the sample size to be adequate for all variables for all ages, also when divided into gender (Table 3).

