## Discussion

In the western world with increasing inactivity and obesity increasing PA in children is a goal in itself. To counteract health related problems in childhood, school-based PA programs may become an important tool [8, 9, 52, 53]. There are studies showing that an increase in PA may simultaneously improve academic performance even without a pedagogical approach included in the activity [54]. A strategy combining academic learning with increased PA may subsequently improve both academic performance as well as physical health in the childhood population [8, 9, 52, 53]. The ability to reach all socioeconomic layers of the population is a great strength of school-based PA programs as it may contribute to reduce social inequalities in health.

Waters et al. demonstrated that child obesity prevention programmes were effective at reducing adiposity, although not all individual interventions were effective [10]. A recent review by Mura et al. assessing 47 school based RCT ‘s on PA interventions also showed promising positive results for cardio-metabolic variables and physical fitness [7]. A longitudinal study permits the intervention to work over time and may create habitual processes in the pupil’s everyday school life.

Lately two Cochrane reports included several studies focusing on health results from schools based RCT’s [9, 52]. Primary outcomes were rate of moderate to vigorous PA (MVPA) during the school day, time in MVPA during school day and time spent in front of a screen. Secondary endpoints were blood pressure, cholesterol levels, BMI, peak oxygen uptake and heart rate [9]. The reports displayed positive health effects, hence school based interventions were recommended [52]. However, as forty-four studies were ranked in four quality levels, none were ranged above “low quality” [9]. The 2013 report showed a positive effect in more time spent in MVPA, less time in front of a screen, higher VO_2max_ and reduction in serum cholesterol values. The effect sizes were small on all outcomes, and Dobbins et al. warn that despite the inclusion of several RCT’s with a large number of participants, a moderate risk of bias is present and any interpretation should be done with caution [9]. Both reports concluded that additional research on the long-term effect is warranted [9, 52]. The longitudinal design in the HOPP-study addresses this issue by allowing follow-up of 6 years for the youngest children.

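### Table 3 labels its 80% power as beta, and its one-sample size of 10 for aerobic capacity cannot support a between-school comparison or the claim of adequacy for every variable, age and gender

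*Protocol article*

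**What the plan says.** The caption of Table 3 (Annual measurements for all participants) states that "the following sample size (intervention and controls schools) was calculated, with a beta of 80% and alpha of 5" per cent. The aerobic-capacity row is 10, footnoted as a one-sample t-test. Most other rows are also one-sample; anthropometry (64) is two-sample, and two rows (126) are marked as Z-score.

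The Intervention analyses section uses a different basis: a parallel-group formula, n per group = 2(σ/Δ)²k, for a "double-sided t-test set at 5% and with test strength 80" per cent, with k = 7.9. No value of σ or Δ is printed for any row. The section nevertheless concludes that "we have determined the sample size to be adequate for all variables for all ages", and extends this to the sample divided by gender.

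Oxygen uptake is measured only in children born in 2008. The section on it says that "the design permits comparison between intervention (*n* = 248) and control (*n* = 103) schools for all years". The Discussion describes a 2013 review of school programmes that found, among other things, higher VO2max, and adds: "The effect sizes were small on all outcomes".

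**The concern.** Beta is the type II error, so the caption contradicts the formula section on the power of the plan.

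The larger issue is what the row of 10 appears to license. Set beside 103 controls, a requirement of 10 makes the oxygen-uptake cohort look ten times larger than necessary. But a one-sample size says nothing about a difference between two groups, and this one is small only because the implied effect is very large. A reader who trusts the adequacy sentence could take a non-significant VO2peak comparison as evidence of no effect on aerobic capacity, when the comparison may simply have been insensitive to a modest one. The same sentence covers every single-grade and gender-split comparison.

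**Working it through.** **Inputs.** Two-sided 5%, 80% power and k = 7.9 (Intervention analyses); sizes and test types (Table 3 and its footnotes); 248 versus 103 (8) Oxygen uptake); grade counts (Table 1). Effects of 0.1 to 0.3 SD are assumed, because the document puts no figure on small.

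**1. Which power was meant.** k = (1.960 + 0.842)² = 7.85, which matches the stated 7.9. With beta literally 0.80, k = (1.960 − 0.842)² = 1.25, which does not. The intended power is 80%.

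**2. Effects behind Table 3.** These have to be back-solved. At 80% power and two-sided 5%, with the footnoted tests:

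| Test | Effect (SD) | n |
|---|---|---|
| One-sample t | 1.0 | 10 |
| One-sample t | 0.6 | 24 |
| One-sample t | 0.5 | 34 |
| One-sample t | 1/3 | 73 |
| One-sample t | about 0.31 | 85 |
| Two-sample t | 0.5 | 64 per group |
| One-sample z | 0.25 | 126 |

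Most rows come out exactly at a round effect, which supports this reading and confirms again that 80% is the power.

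**3. The aerobic row on the two-group formula.** At 1 SD, n = 2 × 1² × 7.9 = 15.8, so 16 per group and not 10. Conversely, 10 per group would need √(15.8/10) = 1.26 SD.

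**4. What 248 versus 103 can detect** (pupils independent, no losses, one year, no adjustment).
- Standard error in SD units: √(1/248 + 1/103) = 0.1172.
- Detectable at 80% power: 2.802 × 0.1172 = 0.328; about 0.33 by noncentral t.
- Split evenly by gender (assumed), 124 versus 51.5: √(1/124 + 1/51.5) = 0.1658, and 2.802 × 0.1658 = 0.465; about 0.47 with the t correction.

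**5. Power at assumed effects.** Power ≈ Φ(d/0.1172 − 1.960).

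| Effect (SD) | Power |
|---|---|
| 0.10 | 13% (14% if the opposite tail is counted) |
| 0.20 | 40% |
| 0.30 | 72% (t), 73% (normal) |

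For 80% power at 0.2 SD with this allocation ratio, about 278 controls would be needed, against 103.

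**6. Other grades.** With the Table 1 counts, power at 0.2 SD within a single grade runs from 40% (103 versus 248) to 51% (154 versus 271), and from 23% to 29% if each grade is split evenly by gender. All grades together (1545 versus 752) give 99%, again ignoring clustering.

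**7. Effect of a richer analysis.** With a baseline and m follow-ups, equal correlation r and a constant effect, the variance is multiplied by (1 + (m − 1)r)/m − r². Power at 0.2 SD for 248 versus 103:

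| r (assumed) | One follow-up | Six follow-ups |
|---|---|---|
| 0.5 | factor 0.75: 50% | factor 0.333: 84% |
| 0.7 | factor 0.51: about 66% | factor 0.26: 92% |
| 0.8 | factor 0.36: 81% | factor 0.193: 97% |

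These figures also assume independent pupils and no losses.

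**The case against.** The strongest reply is that the 40% describes an analysis the protocol need not use. Oxygen uptake is measured every year to 2021, and Analyses of longitudinal effect allows a mixed model for repeated measures with control for baseline values. Step 7 shows that this can bring power at 0.2 SD above 80%. A reader might infer that the design cannot reach 80% power for VO2peak at a small effect; the documents do not show that. Equally, the step 7 figures leave out clustering in nine schools, only two of them controls, and dropout. They do not establish adequacy either.

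Four further points stand in part.
- The implied 1 SD may be on a different scale. Analyses of effect plans a paired comparison, so the one-sample row may concern within-child change. The SD of change is √(2(1 − r)) between-child SDs, so 1 SD of change would be about 0.77 at an assumed r of 0.7 and 0.45 at 0.9. That softens the contrast with small effects, but a within-child calculation still does not size a comparison between schools.
- The remark on small effects describes one cited review. A reader might take it as the protocol's view of all known effects, but the same Discussion also cites a review of 47 trials with promising results for cardio-metabolic variables and fitness. The remark does cover VO2max.
- That the aerobic-capacity row means oxygen uptake is an inference. The Fitness section measures aerobic fitness by an intermittent running test in all pupils. Table 3 has a separate row for general physical capacity, which makes oxygen uptake the more natural reading, though not a certain one. VO2peak is not on the list of primary outcomes, and the running test in the whole cohort would limit any misreading of a null VO2peak result.
- Table 3 did not fix enrolment: all children were invited, and oxygen uptake was limited to one cohort for reasons of time. The issue is what the article claims about sensitivity, not how many children were recruited.

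A reader might also infer from the caption that the study was planned at 20% power. The stated k and the reproduced sizes rule that out.

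**Conclusion.** The point holds as a correction of stated sensitivity. The beta wording is wrong and harmless to the numbers. The size of 10 is a one-sample figure at about 1 SD and does not support the between-school comparison; the protocol's own formula gives 16 per group at that effect. If the row is oxygen uptake, 248 versus 103 detects about 0.33 SD unadjusted in a single year, and about 0.47 SD by gender, ignoring schools and losses. The adequacy sentence, covering all variables, all ages and both genders, is therefore not supported for modest effects in this cohort, or in single-grade and gender-split comparisons generally. The size of the shortfall depends on the assumed effect, on the correlations, and on clustering, none of which the document quantifies. The pooled all-grade comparison is not called into question by this calculation.

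**What to change.** 1. In the Table 3 caption, write power of 80% (beta of 20%).
2. Replace the aerobic-capacity size of 10 with the difference the planned two groups can detect: about 0.33 SD for 248 versus 103, stated as unadjusted and ignoring clustering and losses. Say whether the row means oxygen uptake.
3. In Intervention analyses, limit the adequacy sentence to effects that the actual group sizes can detect, for single-grade and gender-split comparisons generally. Removing oxygen uptake alone would leave the sentence equally unsupported elsewhere.
4. Report the VO2peak comparison with its confidence interval, and say that a non-significant result does not rule out a small effect.

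The cost is a caption, one table entry and two sentences. No pupils, tests or visits are added; the stated sensitivity becomes less favourable.
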